### 6.3 Statistical Methods

**Primary Analyses:** We will examine between-group differences in opioid and BZD exposure associated with an increased risk of falls in the intervention and control groups. Analyses will be performed using the following intention-to-treat principle, and index dates for the intervention group will correspond to the date on which they first received any intervention-related clinical activity. Index dates for otherwise eligible patients from the control group will be chosen at random from each patients' set of clinic visits corresponding to an eligible intervention visit during the study period. Our primary hypotheses are:

- Relative to individuals in both control groups, individuals in both intervention groups will experience a significant reduction in the milligram equivalent exposure to opioids and BZDs during the 1-year follow-up period.

- Relative to individuals in both control groups, individuals in both intervention groups will experience a significantly greater discontinuation rate of opioids and BZDs during the follow-up period 181 to 360 days after index.

There are two overlapping groups of patients aged 65+ that will be included in this study: opioid users and BZD users. For each hypothesis, there will be separate models comparing the impact of the program on opioid users and BZD users. Patients who use both will appear in both models. To examine any differential impact of the program among patients who use both classes of medications, a sensitivity analysis will be performed and will include an indicator variable for patients who use both classes.

Generalized estimating equations (GEE, PROC GENMOD) will be used to create longitudinal pre-post model for the milligram equivalent exposure models. An identity link with a normal distribution will be used for milligram equivalent exposure. The functional form of the model is as follows:

$$\text{Eq. 1: } Y = \beta_0 + \beta_1 X_{\text{exp}} + \beta_2 X_{\text{period}} + \beta_3 X_{\text{exp} \times \text{period}} + \beta_n X_n + \epsilon$$

Where  $X_{\text{exp}}$  is the exposure group indicator,  $X_{\text{period}}$  is the pre-post indicator, and  $X_{\text{exp} \times \text{period}}$  is the period-by-treatment interaction indicator and, correspondingly,  $\beta_3$  is the parameter of the difference in outcome by period for the intervention group compared to the control.  $X_n$  represents a vector of covariates.

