**Secondary Analyses:** Our secondary hypothesis is:

- Relative to individuals in both control groups, individuals in both intervention groups will experience a reduction in the risk of experiencing a fall following the index date.

Risk is operationalized as the odds of experiencing a fall in the 12-month post-index compared to the 12 months pre-index. The models used for this analysis match those in Equation 1, with the exception that the models for fall risk will use a log link with a binomial distribution instead of an identity link with a normal distribution.

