## 6.4 Sample Size and Power:

### 6.4.1 Milligram equivalent exposure to opioids

Effect of various interventions on milligram equivalent exposure to opioids has shown mean reductions ranging from 31% to 49%. A GEE model (continuous outcome) with a total sample size of 3000 patients, each measured two times before and after intervention will have statistical power in the range of 0.865-0.999 to detect differences in means of 0.30 or higher in milligram equivalent exposure when the standard deviation is in the range of 1 to 3. Pre-period measurements will include the 12-month period prior to index, and post-period measurements will include the 12 months following index. This assumes that the baseline correlation between observations is 0.2 or higher and a 20% attrition rate will be observed. Another assumption is that we will assign subjects randomly to an intervention group and control group with an equal split between the two groups. Notably, if the standard deviation of observations is above 3.0 or if the attrition rate is greater than 20%, then our statistical power will drop significantly. All calculations were performed using PASS Software.

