## **6.6 Control of Bias**

Both statistical controls and design elements are used to control for bias in the measurement of study outcomes. The longitudinal pre-treatment post-treatment design helps to control for natural rate of deprescribing in a prevalent user population.

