## **6.7 Handling of Missing Values**

We will apply no imputation method to this data. All data are observational, and randomization should balance missingness across samples. As such, it is unlikely that missing values will create selection bias. Additionally, our chosen statistical method allows for estimation of longitudinal effects even if patients have a missing outcome value.

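### As written, Eq. 1 leaves the dose effect unadjusted for baseline covariates, and the dual-user analysis cannot show a differential effect, because neither specifies a period interaction

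*Protocol*

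**What the plan says.** Section 6.3 (Primary Analyses) writes out the functional form of the dose model. Its terms are an intercept, group, period, group by period, and one additive covariate term, where X_n "represents a vector of covariates". On link and distribution it says "An identity link with a normal distribution will be used for milligram equivalent exposure". The coefficient of interest, β3, "is the parameter of the difference in outcome by period for the intervention group compared to the control". Section 6.4.1 fixes the two periods: "Pre-period measurements will include the 12-month period prior to index, and post-period measurements will include the 12 months following index". No covariate-by-period term is written anywhere.

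The same section plans a sensitivity analysis on whether the programme works differently in patients taking both drug classes. The model for it "will include an indicator variable for patients who use both classes"; no interaction is mentioned.

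Section 6.6 says: "Both statistical controls and design elements are used to control for bias in the measurement of study outcomes". The only mechanism it explains is the pre-post design. For falls, section 6.3 (Secondary Analyses) says "The models used for this analysis match those in Equation 1", apart from a log link and a binomial distribution.

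**The concern.** A reader of Eq. 1 will take the dose effect to be adjusted for whatever baseline covariates are listed. In a two-period identity-link model whose effect is the group-by-period term, additive baseline covariates explain the level of dose, not its change, and β3 is a statement about change.

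Simple random allocation of 20 clinics, ten per arm, across family medicine, primary care and geriatric practices can leave the arms unequal in factors that predict how dose would drift anyway. Covariate adjustment is the usual way to correct such imbalance and gain precision, and under this form it does neither for the dose effect. An SAP may name the covariates, but a longer list of baseline variables under the same form would not help.

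The dual-user analysis has the same flaw more visibly: its stated purpose is to examine a differential effect, and an added indicator does not estimate one.

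**Working it through.** **The plan's own figure.** The only number given for the opioid dose model is its power, 0.865 to 0.999 (section 6.4.1: difference 0.30, SD 1 to 3, correlation 0.2, 3,000 patients). The lower end reproduces with two measures averaged on each side and 1,500 patients per arm:

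- SD of change = 3 × √(1 − 0.2) = 2.683
- SE = 2.683 × √(2/1500) = 0.0980
- 0.30/0.0980 = 3.062, so power = Φ(3.062 − 1.960) = 0.865

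No covariate enters this figure, so it neither supports nor contradicts the point. That it uses all 3,000 patients without loss is a separate matter.

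**Algebra.** Let g be the group indicator and X a covariate fixed at or before index, with coefficient γ.

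- E[pre] = β0 + β1·g + γX
- E[post] = β0 + β1·g + β2 + β3·g + γX
- E[post − pre] = β2 + β3·g

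γX cancels. With complete pairs, the estimate of β3 is the mean change in intervention minus the mean change in control, whatever X is. If X also has a period interaction with coefficient δ, then E[post − pre] = β2 + β3·g + δX, and β3 is adjusted for X.

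**Numerical check.** Eq. 1 was fitted by GEE to simulated data: 3,000 patients in 20 clinics, with age and dual use unbalanced between arms. The settings are illustrative assumptions.

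| Setting | β3, no covariates | β3, main effects |
|---|---|---|
| Complete pairs, baseline covariates | -2.308332 (SE 0.41460) | -2.308332 (SE 0.41460) |
| About 21% of post values lost at random, independence | -2.338 | -2.319 |
| Same, exchangeable, patient clusters | -2.260 | -2.259 |
| About 26% lost, depending on covariates and arm, independence | -2.779 | -2.340 |
| Same, exchangeable, patient clusters | -2.414 | -2.260 |
| Complete pairs, covariate that changes after index and differs by arm | -0.680 | -2.326 (with that covariate) |

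The first row shows patient clusters. With clinic clusters the SE was 0.36388 in both columns. Estimates were identical to six decimals under independence and exchangeable working correlation.

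When dual use was made to change the dose trend (complete pairs), main effects left β3 at -2.896, while covariate-by-period terms moved it to -2.381.

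**Precision, illustrated.** In a second simulation (20 clinics of 150, no true arm effect, clinic type assumed to drive trend), β3 was -0.118 with clinic-clustered SE 0.110, both without covariates and with clinic type and age as main effects. With period interactions it was -0.030, SE 0.040.

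**Chance imbalance, illustrated.** Assume 6 of the 20 clinics are of one type. A 10:10 split gives 3 and 3 with probability C(6,3)·C(14,7)/C(20,10) = 20 × 3432/184756 = 0.372. So a difference of at least two clinics, or 20 percentage points, has probability 1 − 0.372 = 0.628. If that type's natural change differs by 0.5 SD (assumed), β3 shifts by 0.20 × 0.5 = 0.10 SD. The planned effect at the largest SD is 0.30/3 = 0.10 SD.

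**Dual users.** Let D be the dual-use indicator. As planned, D enters like X above and cancels. In a simulation built with a true differential effect, adding D left β3 at -0.195452. A differential effect is the coefficient θ in E[post − pre] = β2 + β3·g + δD + θ·g·D, which needs an indicator-by-group-by-period term.

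**The case against.** **The covariate list is open.** The protocol does not say that X_n is limited to baseline values or excludes product terms, and such detail often goes to the SAP. This stands: a covariate that changes between periods does not cancel. But its post-index value is post-randomisation and may itself respond to the programme, so it is not a safe means of adjustment. An SAP could add product terms; the form written in 6.3 contains none.

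**Outcomes will be missing.** Section 6.4 assumes 20% attrition, and section 6.7 keeps incomplete pairs because "our chosen statistical method allows for estimation of longitudinal effects even if patients have a missing outcome value". This also stands: when loss depends on covariates and arm, main effects do move β3. A reader might infer that the covariates do nothing at all, and the documents do not support that. How many pairs will be incomplete is unclear, since the protocol does not say whether no prescription counts as zero dose.

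**Section 6.6 is not shown to be false.** A reader might infer that it claims a protection the model lacks. It does not tie its statistical controls to X_n, and the group and period terms are themselves a control that removes fixed level differences.

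**Chance imbalance is not bias.** Clinics are randomised. Re-randomising the clinic-type scenario 5,000 times gave a mean β3 of -0.001, and a clinic-level test rejected in 5.2%. This stands: the loss is of precision, and of the chance to correct the imbalance that actually occurs. An unadjusted difference-in-differences is a legitimate analysis, but the plan should not present it as covariate-adjusted.

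**Conclusion.** The point holds for the opioid and BZD dose models. For covariates fixed at or before index and patients seen in both periods, the additive term in Eq. 1 leaves β3 and its robust standard error exactly unchanged. Under loss unrelated to the covariates the change in β3 was at most 0.02 against a standard error near 0.49. In effect the dose result is unadjusted for baseline factors that predict dose trend. The dual-user analysis, specified with an indicator alone, cannot answer its own question; this is the firmest consequence in the text.

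The size for this trial cannot be stated. The 0.10 SD shift and the fall in standard error from 0.110 to 0.040 rest on assumed clinic mix and trend differences and are illustrations only. Nor should exact cancellation be read across to the falls model: in a log-binomial check with complete pairs, a fixed main effect moved β3 slightly, from -0.154 to -0.147. Discontinuation is not covered by this argument. The change is worth making because it is cheap, but the dose analysis is not invalid without it.

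**What to change.** - **Section 6.3, dose models:** replace the additive covariate term with a small set of covariates fixed at or before index, each entered with its interaction with period. Limit clinic-level covariates to two or three, given 20 clinics.
- **Section 6.3, dual-user analysis:** fix the indicator at or before index. Add its three-way term with group and period, plus the lower-order terms (indicator, indicator by group, indicator by period). Report the three-way coefficient with its interval; β3 then refers to single-class users.
- **Section 6.6:** say that covariate control of the dose effect comes through the period interactions, and that the pre-post contrast handles fixed differences in level.
- **Falls model:** the same form may be used for consistency, without claiming that it cures the same exact cancellation.

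The cost is a few lines of text, a few clinic-level degrees of freedom and a little more analysis work. No new data are needed.

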## 6.4 Sample Size and Power:

### 6.4.1 Milligram equivalent exposure to opioids

Effect of various interventions on milligram equivalent exposure to opioids has shown mean reductions ranging from 31% to 49%. A GEE model (continuous outcome) with a total sample size of 3000 patients, each measured two times before and after intervention will have statistical power in the range of 0.865-0.999 to detect differences in means of 0.30 or higher in milligram equivalent exposure when the standard deviation is in the range of 1 to 3. Pre-period measurements will include the 12-month period prior to index, and post-period measurements will include the 12 months following index. This assumes that the baseline correlation between observations is 0.2 or higher and a 20% attrition rate will be observed. Another assumption is that we will assign subjects randomly to an intervention group and control group with an equal split between the two groups. Notably, if the standard deviation of observations is above 3.0 or if the attrition rate is greater than 20%, then our statistical power will drop significantly. All calculations were performed using PASS Software.

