## 6 STATISTICAL CONSIDERATION

Statistical considerations are described below for the primary and secondary outcomes from the cluster-randomized trials. No statistical analysis will be conducted with focus groups, and the surveys will be analyzed using descriptive statistics and bivariate assessments for pre-post change in provider knowledge, skills, and attitudes in management of opioids and BZDs between intervention and control clinics.

All hypothesis tests that are observed and deemed to be not statistically significant will be reported as being inconclusive. All statistical estimates of population parameters will be tabulated along with corresponding confidence intervals (CIs) and/or standard errors (SE). All hypothesis tests and tests for power are two-sided with an overall alpha of 0.05, unless otherwise specified.

**6.1 Primary Outcomes: Opioid and BZD exposure,** as defined by changes in milligram equivalents over time across control and intervention groups as well as discontinuation of opioids or BZDs. Outcomes are described in more detail in Section 6.3.

**6.2 Secondary Outcomes: Risk of Falls,** as defined by differences in rate of falls over time across control and intervention groups and described in more detail in Section 6.3.

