### 6.4.2 Discontinuation rate of opioids

According to a recent systematic review of literature, most opioid continuation rates are from relatively unreliable studies and can be anywhere between 54% to 100%. However, a recent study has found the odds ratio of opioid discontinuation in control versus treatment group to be 1.5 (95% CI [1.0-2.1]). If clinics are randomly assigned to a treatment group and a control group, with an equal number of patients in both groups, a GEE model (binary outcome) with a total sample size of 3000

patients, each measured two times before and after intervention, will have statistical power in the range of 0.631-0.953 to detect differences in odds ratios in the range of 1.30-2.0. There is significant drop in power for detecting differences in odds ratios below 1.3. Baseline probabilities in the treatment and control group are assumed to be in the range of 0.020-0.050 and we assumed a 20% attrition rate. For lower baseline probabilities of 0.010 in each group, the statistical power is in the range of 0.485-0.860 for detecting odds ratios of 1.3 or higher.

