### **6.4.3 Milligram equivalent exposure to BZDs**

Effect of various interventions on milligram diazepam equivalent per day exposure to BZDs has shown mean reductions ranging from 25% to 85%. If clinics are randomly assigned to a treatment group and a control group, with an equal number of patients in both groups, a GEE model with a total sample size of 3000 patients, each measured two times before and after intervention, will have statistical power in the range of 0.678-0.969 to detect differences in means of 0.25 or higher in milligram equivalent exposure when the standard deviation is below 2. Pre-period measurements will include the 12-month period prior to index, and post-period measurements will include the 12 months following index. This assumes that the baseline correlation between observations is 0.2 or higher and that we will observe a 20% attrition rate. Power increases for larger mean difference values and drops significantly at higher standard deviation values.

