### **6.4.4 Discontinuation rate of BZDs**

A systematic review of literature has demonstrated discontinuation rates between 27-80% for interventions to reduce exposure to benzodiazepines. If clinics are randomly assigned to a treatment group and a control group, with an equal split between the two groups, a GEE model with a total sample size of 3000 patients, each measured two times before and after intervention, will have statistical power in the range of 0.859-1.000 to detect differences in post-intervention event probabilities in the range of 0.25-0.85. There is significant drop in power for detecting group differences below 0.25. Baseline probabilities in the treatment and control group are assumed to be in the range of 0.010-0.050 and we assumed a 20% attrition rate.

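### The power figures in Protocol 6.4.1 to 6.4.4 contradict one another and do not follow from their stated inputs

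*Protocol*

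**What the plan says.** Section 6 sets the error rate: "All hypothesis tests and tests for power are two-sided with an overall alpha of 0.05, unless otherwise specified". Section 6.3, Eq. 1, tests dose through the period-by-treatment coefficient, which "is the parameter of the difference in outcome by period for the intervention group compared to the control".

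The four power statements each assume 3,000 patients in total, two equal arms and 20% attrition:

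- **6.4.1, opioid dose:** the set-up is "A GEE model (continuous outcome) with a total sample size of 3000 patients, each measured two times before and after intervention". For SD 1 to 3 and correlation 0.2 or higher, the section claims that this design "will have statistical power in the range of 0.865-0.999 to detect differences in means of 0.30 or higher in milligram equivalent exposure". On the windows: "Pre-period measurements will include the 12-month period prior to index, and post-period measurements will include the 12 months following index".
- **6.4.2, opioid discontinuation:** the model "will have statistical power in the range of 0.631-0.953 to detect differences in odds ratios in the range of 1.30-2.0", with baseline probabilities 0.02 to 0.05. At baseline 0.01 the stated range is 0.485 to 0.860. No correlation is given.
- **6.4.3, BZD dose:** "statistical power in the range of 0.678-0.969 to detect differences in means of 0.25 or higher in milligram equivalent exposure", with SD below 2 and correlation 0.2 or higher.
- **6.4.4, BZD discontinuation:** "statistical power in the range of 0.859-1.000 to detect differences in post-intervention event probabilities" from 0.25 to 0.85, with baseline 0.01 to 0.05. It adds that power falls off markedly for differences under 0.25. No correlation is given.

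The dose effects of 0.30 and 0.25 follow cited mean reductions of 31% to 49% and 25% to 85%. Section 5 defines discontinuation as no prescription in days 181 to 360 after index.

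**The concern.** Sections 6.4.1 and 6.4.3 describe the same design with the same N, split, correlation and attrition. Power then depends only on the difference divided by the SD, yet the section with the smaller standardised effect reports the higher power. At least one of them must be wrong, whatever formula was used. The discontinuation figures look too high in 6.4.2 and too low in 6.4.4.

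These are the only quantitative support the protocol gives for its two primary outcomes in two drug classes. If the optimistic figures are wrong, the sponsor is relying on sensitivity that the design does not have, and a null result would be harder to interpret than the protocol implies.

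**Working it through.** **Inputs.** 3,000 patients, equal split and 20% attrition (6.4.1 to 6.4.4) give 1,500 × 0.8 = 1,200 per arm. Alpha is 0.05 two-sided (6). Correlation is 0.2, the least favourable stated value (6.4.1, 6.4.3). Clustering is ignored throughout, as in the protocol's own text.

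**Step 1: consistency, no formula needed.** 6.4.1: 0.30/3 = 0.10 SD, power 0.865. 6.4.3: 0.25/2 = 0.125 SD, power 0.678. Both cannot hold.

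**Step 2: dose, one pre and one post value.** For the Eq. 1 interaction, SE = SD × √(2(1 − ρ)) × √(2/n) and power = Φ(difference/SE − 1.96).

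- BZD, SD 2: SE = 2 × 1.2649 × √(2/1200) = 0.1033; 0.25/0.1033 = 2.421; power = Φ(0.461) = 0.678. This is the protocol's figure.
- Opioid, SD 3: SE = 3 × 1.2649 × √(2/1200) = 0.1549; 0.30/0.1549 = 1.936; power = Φ(−0.024) = 0.491. The protocol says 0.865.
- Opioid, SD 1: power exceeds 0.999, so the upper end of 6.4.1 is attainable.

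**Step 3: can another reading give 0.865 for opioid dose at SD 3?**

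| Reading | Power |
|---|---|
| One pre, one post, no attrition (1,500 per arm) | 0.581 |
| Post-period only, 1,200 per arm | 0.688 |
| ANCOVA, 1,200 per arm | 0.705 |
| Two pre and two post values, 1,200 per arm | 0.782 |
| Two pre and two post values, no attrition | 0.865 |
| One pre, one post, 3,000 per arm | 0.865 |
| One pre, one post, 1,200 per arm, correlation 0.68 | 0.865 |
| Time-averaged difference, 1,200 per arm | 0.885 |

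Each row that gives 0.865 changes a stated input: the attrition, the total N or the correlation. The time-averaged test is not the Eq. 1 interaction, and it puts 6.4.3 at 0.977, so it does not reconcile the sections. Two pre and two post values with attrition put the 6.4.3 lower bound at 0.928, not 0.678. None of these set-ups yields both printed lower bounds.

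**Step 4: opioid discontinuation.** Convert the OR to a second probability, then power = Φ(|p1 − p0|/√[(p0(1 − p0) + p1(1 − p1))/n] − 1.96), with n = 1,200.

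| Base p0 | p1 at OR 1.3 | Power, OR 1.3 | Stated lower bound | Power, OR 2.0 |
|---|---|---|---|---|
| 0.01 | 0.0130 | 0.100 | 0.485 | 0.509 |
| 0.02 | 0.0258 | 0.158 | 0.631 | 0.793 |
| 0.05 | 0.0640 | 0.317 | 0.631 | 0.990 |

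Reaching 0.631 would take about 6,900 per arm at base 0.02 or 2,870 at base 0.05. Reaching 0.485 at base 0.01 would take about 9,570 per arm. At the OR of 1.5 that 6.4.2 cites from a recent study, power is 0.33 to 0.66 for bases 0.02 to 0.05.

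A literal pre-post interaction on the log odds (one pre, one post, correlation assumed 0.2 to 0.5) is lower still: 0.11 to 0.15 at base 0.02 and 0.21 to 0.30 at base 0.05.

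**Step 5: BZD discontinuation.** From base 0.05, a 0.25 difference has SE √[(0.0475 + 0.21)/1200] = 0.0146; 0.25/0.0146 is about 17, so power exceeds 0.999, against the stated 0.859. A 0.03 difference already has power 0.847 (base 0.05) to 0.997 (base 0.01), so the stated drop below 0.25 does not follow.

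**The case against.** **The count of measurements is ambiguous.** The wording in 6.4.1 can be read as two values before and two after, which gives exactly 0.865 at 1,500 per arm. The mistake may then be no more than attrition left out, and the corrected figure is 0.78 rather than 0.49. This stands as a possibility. The single 12-month windows and the two-level period term in Eq. 1 favour one value each side, and on either reading 0.865 does not follow once the stated attrition is applied.

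**The two-proportion test is a substitute.** The Protocol Synopsis describes discontinuation as a longitudinal pre-post analysis, and 6.4.2 assumes a binary GEE with no correlation given. So 0.16 to 0.32 cannot be called the correct value of the protocol's own calculation. This stands; irreproducible and implausibly high is the fair description. At base 0.05 some favourable set-ups come near or pass 0.631 (0.650 with 3,000 per arm; 0.843 with four uncorrelated measures, time-averaged). None tried reaches 0.631 at base 0.02, and at base 0.01 the highest two-sided value is 0.331 against 0.485.

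**Percentages as milligrams.** A reader might infer that proportions were entered as milligrams. The numbers suggest it, but the protocol does not say so. A 0.30 difference with SD 1 to 3 is coherent if dose is scaled to its baseline mean, in which case only the unit label is wrong. What the text does show is that the effect is not tied to the analysed scale: no mean or SD in milligram equivalents is given.

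**N was not derived from these powers.** Section 4.2 takes all eligible patients in 20 clinics, so no enrolment decision turns on them.

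**Conclusion.** The point holds. Sections 6.4.1 and 6.4.3 cannot both be right. On the Eq. 1 test with 1,200 per arm and correlation 0.2, the 6.4.3 lower bound is right at 0.678, while opioid dose at SD 3 has about 0.49 (0.78 with two values each side) instead of 0.865. The 6.4.2 lower bounds cannot be reproduced and lie well above a simple two-arm comparison: about 0.16 to 0.32 against 0.631, and 0.10 against 0.485. The definition of discontinuation also has no natural pre-period value, since it looks only at days 181 to 360 after index in patients who are users at baseline. Section 6.4.4 understates power, so that error is conservative.

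A reader might take 0.49 or 0.16 to 0.32 as the trial's real power, or conclude that every stated figure is wrong. Neither is supported. The 6.4.3 lower bound and the 6.4.1 upper end stand. The recomputed values also ignore clustering and assume 1,200 users per arm in each model, although 6.3 fits separate models to overlapping groups of opioid and BZD users. As an illustration only, with an assumed intraclass correlation of 0.01 to 0.05 for the change and 2,400/20 = 120 evaluable patients per clinic, the design effect is 1 + 119 × ICC = 2.19 to 6.95, and 0.49 would fall to about 0.26 to 0.11. In the other direction, discontinuation power at OR 1.3 rises if the control rate is higher: 0.53 at 0.10 and 0.67 at 0.15.

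**What to change.** Rerun the four calculations for the analyses actually planned and replace the ranges in 6.4.1 to 6.4.4:

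- **Dose:** power for the Eq. 1 interaction on the analysed scale, using the mean and SD of MME and DME exposure from the EHR, with the cited percentage reductions converted to that scale.
- **Discontinuation:** a two-arm comparison of the risk of discontinuation in days 181 to 360 after index, at a stated control rate. Align the Synopsis wording with it.
- **All four:** use the number of evaluable opioid users and BZD users per arm, apply attrition and allow for clustering by clinic. Print the number of measurements before and after index, SD, correlation where one is used, intraclass correlation, alpha and n per arm.

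The cost is about a day of statistician time, an EHR query and a protocol text change. Some stated powers will fall and the BZD discontinuation figure may rise. Enrolment need not change.
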